#### Control population

For our statistical approach as outlined below, we request data from the Federal Statistical Office to provide a nationwide comparability. We will use data on length of hospital stay. Age, gender, health care insurance, place of residence, main diagnosis, comorbidities, and study center will be used for statistical adjustment.

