### Endpoints

All patients will be daily assessed during hospitalization and contacted 30 days after admission by phone for a structured and blinded interview to assess primary and secondary endpoints.

The primary endpoint of this study is length of hospital stay within 30 days after admission including readmissions during this period (corresponding to Module 1). Length of hospital stay will be verified based on hospital data for the index hospital stay and complemented by 30-day interviews regarding possible secondary hospitalizations.

Secondary endpoints (corresponding to Module 1–3) include measures of patient-oriented outcomes:in-hospital and all-cause 30-day mortalityunplanned readmissions or unplanned general practitioner / ED visitsdelaying factors of ED- and medical ward’s floweffective time to hospital discharge after involving external institutions (time from transfer application to transfer)institutionalizationsatisfaction with ED-, ward-, and discharge processfunctional status (incl. Quality of life) using the EuroQol Group 5-Dimension Self-Report Questionnaire (see Additional file 1) [23].

To study hospital internal processes and effects of interprofessionality, we will look at compliance and agreement of the three health professions (physicians, nursing, and social workers) in the use of “In-HospiTOOL”, and delays from the anticipated to the effective discharge date as compared to discharge date anticipated by the different health care professionals on admission and during the course of the hospital stay. We will use the above-mentioned outcome data set as benchmark to establish a risk-adjusted resource and quality cockpit to compare different hospitals and demographics (corresponding to Module 3).

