#### User-oriented key data benchmarking

Based on the sounding board consensus, we designed a structured questionnaire (see Additional file 2) to perform phone interviews with all included patients 30 days after hospital admission to assess their outcome data and satisfaction. Each study site establishes a local interview team performing the 30-day structured follow-up interviews. Depending on the cumulative number of patients, between 3 and 7 part-time working persons were recruited by each study site, respectively, and were finally instructed by the core study nurse team.

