#### Difference in differences

To quantify an overall effect on length of hospital stay after implementing the “In-HospiTOOL”, we fit a patient-level multivariate linear regression model. It will include lengths of hospital stay of “control” hospitals, all risk adjusters listed above in the manuscript, and a time variable for study weeks. The dependent variable will be length of hospital stay (days in hospital). We will test for interaction between the intervention period and the intervention population and will assess whether there is a difference in the change (slope) in length of hospital stay over time between the two study populations. The intervention and control groups will have different baseline characteristics, however both groups will be exposed to similar alterations in outcomes over time without the interventional program.

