Our study has several potential limitations. First, inclusion of about 35`000 patients over the 18-month study time frame is ambitious. However, based on our large experience from previous multicenter studies, a well-established multicenter research network, and the high prevalence of hospitalized multimorbid patients eligible for this trial, we are convinced that the trial is feasible. The second limitation of this trial is the lack of randomization. Methodologically, in a trial whose intervention focuses on the process of care, neither patient-level randomization nor a randomized cross-over design was feasible as a carry-over effect would have biased the control group. For a cluster randomized trial, a large number of similar clusters (i.e. hospitals) would be needed – which is challenging in Switzerland particularly in light of the limited study budget. Therefore, we chose an ITS model in a quasi-experimental study design using administrative data from non-participating hospitals as a control group. Doing so, we account for differences in the patient population that may occur due to epidemiological variations. Third, as a pragmatic trial with a bundled intervention, it will be challenging to understand which part of our intervention shows clinical effects, leading to potential participation bias. Nonetheless, the large amount of health care data collected will also allow to provide scientific evidence as to which elements of patient management are influenced by the intervention.

In conclusion, this pragmatic comparative effectiveness health services research trial will inform whether the implementation of a novel electronic tool for inpatient management optimizes inter-professional collaboration and thereby reduces length of hospital stay without derogating subjective and objective patient-oriented measures. Our trial will help to compare between diverse transition processes within seven different hospitals and to create a benchmarking for inpatient care quality. This study synergizes national networks and, thus, has the potential to become a cornerstone in the present public healthcare discussion.

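### The 30-day primary endpoint, with readmissions taken from a phone interview, is not reconciled with the control data or with the outcome of the difference-in-differences model

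*Protocol article*

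**What the plan says.** The Endpoints section of the protocol article sets the outcome: "The primary endpoint of this study is length of hospital stay within 30 days after admission including readmissions during this period". Index-stay days come from hospital data, "complemented by 30-day interviews regarding possible secondary hospitalizations". The interviews cover the included study patients. The section User-oriented key data benchmarking says who does them: "Each study site establishes a local interview team performing the 30-day structured follow-up interviews".

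For the comparison group, the Control population section says "we request data from the Federal Statistical Office to provide a nationwide comparability" and then "We will use data on length of hospital stay". The limitations paragraph of the Discussion describes the design as "using administrative data from non-participating hospitals as a control group". Neither place mentions readmissions, a 30-day window, linkage of stays or an interview for controls.

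The section Difference in differences enters the stays of control hospitals into a patient-level model and says "The dependent variable will be length of hospital stay (days in hospital"). It does not say whether this is the index stay or the 30-day total. The analysis plan calls difference in differences and the interrupted time series complementary, and the time-series section then labels the latter a sensitivity analysis.

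**The concern.** The article fixes three things that do not fit together: an endpoint with a readmission component, a source for that component that exists only in the study hospitals, and a controlled model fed with control data described only as length of stay. Two readings are open, and neither delivers a controlled estimate of the declared endpoint.

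- **Reading A.** Study patients carry the 30-day total and controls carry something measured differently. The readmission part of the contrast is then a before-after comparison inside the study hospitals. It is exposed to any change over time in interview response or recall and, if controls carry no readmission days at all, to secular change in readmissions.
- **Reading B.** The model uses index stay in both groups. This compares like with like, but the declared primary endpoint gets no controlled analysis. The tool aims at earlier discharge, so days that return as readmissions are what the 30-day definition is there to catch, and reading B would miss them.

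The design is not randomised, and the article relies on the control group to separate the tool's effect from background change.

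**Working it through.** The article gives no effect size, standard deviation, readmission rate or interview response rate, so there is no figure of its own on this point to reproduce. The structure comes from the document; the sizes below are assumptions.

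**From the document.** Study-hospital outcome: index days plus interview-reported readmission days. Control outcome: length of stay.

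**Assumed.** A share p of 5% to 15% of patients is readmitted within the window, for d = 4 or 8 days each. Readmission days per patient are r = p × d, from 0.05 × 4 = 0.20 to 0.15 × 8 = 1.20. Patients not captured by the interview contribute no readmission days.

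**Formula.** DiD = (T1 − T0) − (C1 − C0), where 0 is the observation phase and 1 the intervention phase. Under reading A, T = index days + r × capture, and C = index days. Index days are unchanged in steps 1 to 3, so the true effect there is zero.

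1. *Constant gap.* With r and capture the same in both phases, T1 − T0 = 0 and C1 − C0 = 0. The bias is 0.00 days.
2. *Secular fall of 10% in readmission days in both groups, full capture.* T1 − T0 = 0.9r − r = −0.10r. Controls show 0 because their readmission days are not counted. The spurious DiD is −0.10r.
3. *Interview capture falls from 80% to 70%, readmissions unchanged.* T1 − T0 = 0.7r − 0.8r = −0.10r. The spurious DiD is again −0.10r. A rise in capture would reverse the sign.
4. *Reading B. The tool cuts index stay by 0.30 days and raises readmission days by 20%.* The index-only DiD is −0.30. The declared endpoint would give −0.30 + 0.20r.

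| r (days) | Step 2: secular fall | Step 3: capture falls | Step 4: declared endpoint | Step 4: index only |
|---|---|---|---|---|
| 0.20 | −0.02 | −0.02 | −0.26 | −0.30 |
| 0.40 | −0.04 | −0.04 | −0.22 | −0.30 |
| 0.60 | −0.06 | −0.06 | −0.18 | −0.30 |
| 0.80 | −0.08 | −0.08 | −0.14 | −0.30 |
| 1.20 | −0.12 | −0.12 | −0.06 | −0.30 |

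If readmission days for controls did come from linked administrative records while study patients kept the interview, step 2 would cancel, since both groups would fall by 0.10r. Step 3 would not, because capture changes in one group only. What matters is therefore a common source as well as a common definition.

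**The case against.** The strongest reply is that a condensed article need not specify the data extract. The wording on control data does not say that length of stay is all that will be used, and the article is silent on whether stays of one patient can be linked. The model's dependent variable can also be read as shorthand for the endpoint already defined. This stands in part: a reader might infer that the endpoint cannot be built for controls, and the text does not show that. It shows only that no construction is given. Nor does the article itself call difference in differences primary; that follows from the label given to the time series.

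Other inferences also go too far.

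- A reader might think that unequal definitions alone invalidate the contrast. They do not: step 1 shows that a constant gap cancels.
- A reader might think that the 30-day limit shortens long stays in one group only. Truncating control stays at 30 days needs nothing beyond length of stay, and the article does not rule it out.
- The interview is described as "contacted 30 days after admission by phone for a structured and blinded interview to assess primary and secondary endpoints", and local interviewers may be able to infer the phase from the calendar. That is a separate question and lends no weight here.

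The sizes rest on assumed rates, and the capture scenario also needs unreached patients to count as having no readmission days, which the article does not say. A readmission change caused by the tool belongs to the effect; it is bias only where it is secular.

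What the reply does not remove is the mismatch among things the article does state. The interview is the named source of readmission days, and control patients do not receive it. More detail alone cannot settle this; someone must choose one outcome and one source.

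**Conclusion.** The point holds as a mismatch between the declared endpoint, the control data and the model outcome. As written, the main controlled analysis either compares differently measured outcomes or leaves the declared primary endpoint without a controlled analysis. The time-series section offers no way round this, because it too draws on control lengths of stay.

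Under the assumed 0.2 to 1.2 readmission days per patient, a 10% secular fall with no readmission days counted for controls, or a ten-point drop in interview capture, produces about −0.02 to −0.12 days with no true effect. An index-only analysis would report −0.30 days where the declared endpoint would show −0.06 to −0.26, if the tool raised readmission days by 20%. With stable readmissions and stable capture, the bias under the first reading is zero. Because the article states no target effect, it does not show how large these shifts are against the effect sought. The need to settle one outcome does not depend on them: left open, the choice could be made after results are seen.

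**What to change.** State one outcome for the controlled analysis, computed identically from routine case data in both groups and all phases, with the same 30-day truncation, and use it in the Endpoints, Control population and Difference in differences sections.

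- **If the Federal Statistical Office extract can link stays of one patient:** use 30-day hospital days including readmissions in both groups, from those records.
- **If it cannot:** name index-stay length, truncated at 30 days in both groups, as the outcome of the controlled analysis. Report interview-based 30-day days alongside it as an uncontrolled comparison within the study hospitals, so that offsetting readmissions stay visible.

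The cost is revised wording and one more item in the data request. Without linkage there is a real loss: the controlled analysis answers a narrower question than the declared endpoint, and the readmission component has no control group. The text should say so.

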### Theoretical aspects, hypothesis

#### Module 1 resource (mis-)utilization & allocation

We hypothesize that implementing the “In-HospiTOOL” in a nationwide multicenter setting will significantly shorten length of hospital stay without compromising patient outcomes and functional independence. Systematic early determination of clinical stability, estimation of the post-acute care referral probability (using the Post-acute care discharge [PACD] score [15]), fixing a possible discharge date after initial ED assessment as well as a tight interprofessional collaboration enabled through an electronical communication platform (“Visitentool”, Fig. 1) will result in decreased waiting times contributing to the shortening of length of hospital stay [16–18].

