**Fig. 1 Fig1:**
[figure not shown]
The “*Visitentool*” (german for “ward-round tool”). Inter-professional collaboration via an electronical communication platform. Nursing and physician staff as well as social services daily assess the clinical and functional situation about possible discharge (using simple, intuitive color coding) and propose possible discharge dates. Also, reasons for delays in discharge are being monitored

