#### Module 2 Interprofessional collaboration, integral hospital and post-acute patient transition

Transparent and systematic interprofessional communication will reveal factors for delay in these polymorbid patients (pending diagnostics, medical treatments, administrative and organizational elements) throughout the hospital stay. Doing so, we will identify regional and socioeconomic (e.g., health care insurance status) differences in the patient care continuum. We hypothesize that longitudinal observation of patient transition will further allow measurement of effective time from initial request to a post-acute care institution to effective transfer with corresponding internal and external delaying factors (Fig. 2). We will systematically examine patient satisfaction, hypothesizing that it will not decrease upon the study intervention. Implementing a reengineered discharge questionnaire including the teach-back methodology, we aim to improve patient education [19, 20]. This effort will not only strengthen interprofessional coordination and communication, but also increase health care continuity across all hospital transition steps. Moreover, we systematically investigate reasons for low satisfaction.

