### Statistical analysis plan and sample size

The primary analysis population includes all consecutively recruited patients following an intention-to treat (ITT) principle. The number of patients lost to follow-up will be minimized by every effort. The per-protocol (PP) population analysis will be prospectively defined to exclude patients in whom major protocol violations have occurred. Specifically, the following criteria will lead to exclusion from the PP population: major violation of study inclusion or study exclusion criteria, patients with missing information from the In-HospiTOOL forms, or missing follow-up interviews.

We will compare all endpoints between all three study phases in the overall ITT population, the PP population and within predefined subgroups as discussed below. We will analyze all endpoints in an adjusted manner for the main covariates such as age, gender, health care insurance, home of residence, main diagnosis, comorbidities, and study center. Regarding sample size considerations, we include consecutive patients in each hospital over a 6-month period for the observation, implementation, and the intervention period, respectively. Given the large number of patients per study site seen in routine (i.e. between 2`500 and 8`000 polymorbid medical inpatients) per year, we estimate to enroll approximately ~ 35′000 patients over 18 months of recruitment. This large amount of patient data will provide adequate power to investigate the effect of introducing a patient care tool in the overall medical hospitalized patient population and allow for subgroup analyses, as well as important post-hoc analyses.

We will perform two complementary, quasi-experimental analyses to estimate the effect of the intervention: difference in differences and ITS.

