#### Interrupted time series (ITS) model

We will analyze the trends in length of hospital stay from start of observation through the end of the intervention period (18 months). For this purpose, we will conduct an ITS as a sensitivity analysis. We will implement the ITS using generalized estimating equations (GEE), to examine linear trends in weekly, hospital-level, risk-adjusted length of hospital stays. ITS models will be tested for autocorrelation to control for seasonal trends using the Durbin-Watson statistics [25]. We will analyze the change in trend between all three time periods. This approach allows us to distinguish between a possible effect of the intervention and a difference from underlying trends facing both study groups and can also help to analyse whether the intervention effects will sustain over time. We will calculate weekly-adjusted length of hospital stay using linear GEE that includes all lengths of hospital stay from the control and intervention populations and all above mentioned risk factors. We will graph weekly length of hospital stay for all populations over time and use the estimated weekly means for control and intervention patients to assess for a weekly difference between the two groups. Finally, we explore whether the adjusted weekly length of hospital stay decreases in the intervention period and whether there will be an independent time trend effect induced by the intervention only [26].

To summarize, we will use four statistically hypothesis tests during each period: (i) Are there significant trends in length of hospital stay change during the period. (ii) Will the trend differ between the control and intervention populations (the interaction between time and control or intervention conditions) during the period. (iii) Will the trend during the intervention period differ from the trend during the observation period within all three conditions. (iiii) Will the magnitude of the altered trend between the intervention and the observation period differ between the three conditions (the interaction between the change in slope and intervention or control conditions). These models will also be implemented for the analyses of the secondary endpoints.

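### The application-to-transfer wait has a value only for applicants who are finally transferred, so its mean can shift between phases with no change in transfer speed

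*Protocol article*

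**What the plan says.** The Endpoints section of the protocol article lists, as a secondary endpoint, "time to hospital discharge after involving external institutions (time from transfer application to transfer". The Module 2 section describes the same interval as "measurement of effective time from initial request to a post-acute care institution to effective transfer". Both stop the clock at transfer. Neither gives a value for an applicant who dies in hospital or leaves for another destination.

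On the analysis, the section on the statistical analysis plan and sample size states: "We will compare all endpoints between all three study phases in the overall ITT population". For the difference in differences the article says "we fit a patient-level multivariate linear regression model". The interrupted time series uses generalized estimating equations "to examine linear trends in weekly, hospital-level, risk-adjusted length of hospital stays". That section closes with "These models will also be implemented for the analyses of the secondary endpoints". No time-to-event or competing-event method is named.

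Two parts of the tool bear on who applies and who leaves by which route. Module 1 includes an early "estimation of the post-acute care referral probability". The caption of Figure 1 says that nurses, physicians and social services "daily assess the clinical and functional situation about possible discharge". In-hospital mortality and institutionalization are separate secondary endpoints. Length of stay in all patients is the primary endpoint.

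**The concern.** A linear model needs a number for every patient it includes, and here only transferred applicants have one. Whether an applicant is transferred is settled after the tool has begun to act. The comparison between phases is therefore restricted to a group defined by a later outcome, and that group may differ between phases because of the tool.

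The planned covariates are patient characteristics and study center, so they do not correct for selection that happens after application. The section on the control population names only length of stay as the outcome to be used, so no outside series of transfer waits is described that could absorb a shift.

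At stake is how the result is read. A shorter or longer mean wait would naturally be taken as faster or slower transfer, when it may only reflect how many applicants left by another route. The same problem carries into the planned comparison of hospitals, because hospitals may differ in the share of applicants who are transferred.

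**Working it through.** **Inputs.** The article gives no transfer waits, no number of applications and no share of applicants transferred. There is no figure of the plan to reproduce, and every rate below is an assumption.

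**Model.** Let L be the daily transfer rate and M the daily rate of leaving without transfer, both constant. The share leaving without transfer is s = M/(L+M). The mean wait among transferred patients is 1/(L+M) = (1−s)/L.

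**Case 1: L fixed at 1/8 per day (latent mean wait 8 days).**
- s = 10%: 0.9 × 8 = 7.2 days.
- s = 20%: 0.8 × 8 = 6.4 days, a change of −0.8 days; 6.4/7.2 = 0.889, or −11%.
- s = 30%: 0.7 × 8 = 5.6 days; 5.6/7.2 = 0.778, or −22% against s = 10%.
- For latent means of 5 and 12 days, going from 10% to 20% gives −0.5 and −1.2 days, again −11%.

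**Case 2: L fixed at 0.12 per day, M doubled.**
- M = 0.03: mean 1/0.15 = 6.67 days; share transferred 0.12/0.15 = 80%.
- M = 0.06: mean 1/0.18 = 5.56 days; share transferred 0.12/0.18 = 67%. The change is 5.56/6.67 = 0.833, or −17%.
- If transfer also slows to L = 0.11 with M = 0.06: mean 1/0.17 = 5.88 days. This is still below 6.67, so slower transfer looks faster.

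**Case 3: the direction is not fixed.** Take a latent mean of 8 days and s rising from 10% to 20%, but change who leaves.
- Exits at random at the moment of application: no shift. The transferred are a random sample of applicants, with mean 8 days in both phases.
- Quickly placed patients more likely to leave (probability of leaving 2s·e^(−LT), with T the latent wait): the mean among transferred is (1−s/2)/[(1−s)L]. This gives 0.95/0.9 × 8 = 8.44 days and 0.9/0.8 × 8 = 9.0 days, a rise of about 0.55 days.
- Slowly placed patients more likely to leave (probability 2s·(1−e^(−LT))): the mean is (1−1.5s)/[(1−s)L]. This gives 0.85/0.9 × 8 = 7.56 days and 0.7/0.8 × 8 = 7.0 days, a fall of about 0.55 days.

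**How often it would be declared a difference.** The simulation used 1,000 runs per setting and a simple two-sample comparison of means among transferred patients, two-sided 5%. It had no clustering, covariates or time trend. Transfer speed was identical in both phases, and s was 10% against 20% as in Case 1. A difference was declared in 40%, 84% and 99% of runs with 500, 1,500 and 3,000 applications per phase. With s equal in both phases (15%, 1,500 applications) the rate was 5%. With exits at application it was about 4% to 6%. These application counts are assumed. For scale, 35,000 patients over three equal phases is about 11,667 per phase.

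**What using all applicants recovers.** Under the Case 1 model, the cause-specific transfer rate is transfers divided by days waited by all applicants. Per applicant this is 0.9/7.2 = 0.125 in one phase and 0.8/6.4 = 0.125 in the other. The ratio is 1.0, which is the truth, where the mean wait gives 0.889.

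**The case against.** The strongest objection is that handling of non-transferred applicants, for one of several secondary endpoints, is a detail a journal article leaves to the analysis plan. The article nowhere says these patients are excluded. The opening words of the endpoint, about discharge, could be read to include discharge home. The sentence extending the models to the secondary endpoints is generic and also covers mortality and readmission, which are not durations. This has weight, and a fuller plan may deal with the matter. But the bracket in the Endpoints section and the Module 2 text both end the interval at transfer, and the article itself names the class of model. Taken together, these leave the other applicants without a usable value.

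A reader might infer that the tool will send waiting patients home, cause applications to be withdrawn, or repeatedly re-estimate the referral probability. The article supports none of these. It describes an early referral estimate and a daily assessment of possible discharge, which make a change in destination possible and no more. A reader might also infer that the endpoint must show a false speed-up. Case 3 shows that it need not. Earlier or additional applications after the early estimate could also lengthen the interval.

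Two further points stand. Module 2 presents the interval as something to be measured, with its delaying factors, and states no hypothesis that it shortens. And a shift towards death or home discharge may show in the mortality and institutionalization endpoints. That would reveal the problem, but it would not repair the estimate of the wait.

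**Conclusion.** The point holds for this one secondary process endpoint. As defined, and with the models the article carries over, it compares waits among completed transfers only, and membership of that group may differ between phases. The mean can then move without any change in transfer speed.

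Under constant rates with exits spread over the wait, the observed mean falls by about 11% when non-transfer rises from 10% to 20%, and by about 17% when it rises from 20% to 33%. Exits at application give no shift. Selective exit of easily placed patients turns it into a rise of about 0.55 days on a latent mean of 8 days. These sizes rest entirely on assumed rates and on a change in the non-transfer share that the documents do not assert. What does not depend on the rates is that a change in this mean cannot by itself be read as a change in transfer speed, in either direction. The primary endpoint is not affected.

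**What to change.** For this endpoint, define the analysis set as every index-stay patient with a transfer application. Analyse time from application with transfer as the event, and in-hospital death and discharge to another destination as competing events. Count withdrawal as a competing event only if its date is recorded, which the article does not show. Compare the cumulative incidence of transfer and the cause-specific transfer rate between phases, with the covariates already planned. Report, by phase, the number of applications and the share ending in transfer. Keep the mean wait among transferred patients as a descriptive figure only.

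The cost is a short change to the analysis text and a little analysis work, using the application date, discharge date and destination of the index stay. The result is slightly less simple than a mean number of days. Two limits remain. The change does not remove a tool-driven difference in who applies. And if easily placed patients are the ones sent home, the cause-specific rate still describes a selected group of those left waiting, so it should be read beside the cumulative incidence and the competing exits.
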